#### 9.4.2 ANALYSIS OF THE PRIMARY EFFICACY ENDPOINT(S)

Growth velocity, based on anthropometric measures, at each scheduled time point will be summarized using descriptive statistics (mean, SD, median, interquartile range, minimum, and maximum). The test of hypothesis of no change from the baseline in growth velocity and height SDS will be conducted via paired t-test. The measurement of height will be converted to age-and sex-appropriate standard score (SDS) by comparison with the CDC reference standards. The Z-score will be summarized similarly to growth velocity. Additional details of the analysis including management of missing data, and approach to handling outliers, non-adherent and lost to follow up subject data will all be included in a separate statistical analysis plan.

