#### CNP deficiency due to mutations in the *NPPC* gene

To date, 2 families have been identified who have heterozygous mutations in the CNP gene itself (*NPPC*) presenting with dominantly inherited short stature with heights ranging from -4.3 to -2.3 SD. The affected patients were noted to have small hands as well but were otherwise healthy. Both mutations were missense variants (p.Arg117Gly and p. Gly119Cys) affecting highly conserved amino acids in the CNP ring. In vitro studies showed that these missense variants led to decreased cGMP production upon stimulation of the NPR-B receptor in both the homozygous and heterozygous state.

Patients with CNP deficiency in either the heterozygous or homozygous state are natural candidates for vosoritide as CNP replacement therapy. As further evidence to support this concept, Fujii et al. crossed a CNP knockout mouse model (*Nppc*-/-) with a mouse overexpressing a transgene for CNP. The *Nppc*-/- mice demonstrate decreased body length, bone size, and growth plate width. After crossing with the transgenic mice, all of these phenotypic features were greatly improved suggesting that circulating CNP is able to rescue the phenotype of global CNP deficiency.

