#### Patients with heterozygous defects in *ACAN* (the gene that encodes Aggrecan)

Aggrecan is a proteoglycan found in the extracellular matrix of growth plate cartilage. Individuals with heterozygous defects in Aggrecan present with dominantly inherited short stature often with advanced bone ages and premature growth cessation. A chick model of Aggrecan deficiency demonstrated the

[figure not shown]

**Fig. 10.** Phosphorylated MAPK is increased in E6 nm cartilage. (A) Immunoblotting analysis showing levels of phosphorylated MAPK (Erk), and β-actin as a loading control, in E6 wt and nm cartilage lysates. (B) Relative levels of phosphorylated MAPK to β-actin were quantified in three independent experiments. Data was evaluated for statistical significance using the Student's *t*-test. \**p* < 0.04.

absence of extracellular matrix between chondrocytes as well as smaller hypertrophic chondrocytes with premature differentiation of the chondrocytes into the hypertrophic phenotype. Interestingly, this model showed evidence of FGFR3 dysregulation with increased levels of phosphorylated ERK in the mutant cartilage (see Figure). In addition to the inhibitory effect on the ERK pathway detailed above, CNP has also been shown to normalize the decreased extracellular space seen in an achondroplasia mouse model and to increase glycosaminoglycan synthesis in those mice. In a study examining the effects of FGF2 on rat

chondrosarcoma cells, CNP treatment was also able to rescue the loss of extracellular matrix seen after FGF2 administration. Through detailed mechanistic studies, the authors found that CNP inhibited matrix metalloproteinases, proteins that degrade the extracellular matrix components, in addition to stimulating extracellular matrix production. They noted that this effect on matrix production was independent of endogenous FGF2 signaling. Based on these studies, we conclude that vosoritide therapy may be beneficial in patients with Aggrecan deficiency as it will both inhibit the increased ERK phosphorylation seen in Aggrecan deficiency as well as induce increased production of extracellular matrix through FGF2 independent methods.

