### 4.2 SCIENTIFIC RATIONALE FOR STUDY DESIGN

In this study, we are focusing on six specific genetic subgroups causing short stature. These six groups all share a common final pathway of growth inhibition via increased activation of ERK1/2 signaling in the chondrocyte (the pathway targeted by vosoritide). These groups are also each relatively rare and within each group there is significant heterogeneity in the severity of short stature. Therefore, we think it is reasonable to combine the six groups into a single study cohort. To control for the interindividual variability, each subject will serve as his or her own control via the baseline 6 month observation only period. We propose to include up to 75 subjects in order to have at least 10 subjects in each subgroup. As the response to vosoritide therapy in this group is unknown, no formal power calculations are

planned. Rather, this is an exploratory study in a rare disease population, and we seek to obtain initial data which will influence future study planning. Additionally, at this time, it is not feasible to recruit a large enough cohort of any of the specific genetic causes to make this a meaningful study. It is difficult to predict the anticipated distribution of patients between each subgroup. In addition to the whole cohort analysis, exploratory analyses will be performed based on underlying genetic etiology. In the future, a randomized controlled study will be required in order to definitively prove efficacy. That is not the goal of the current study as this is a proof of principle study to assess whether subjects meeting these inclusion criteria have the potential to respond to vosoritide therapy.

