### 5 STUDY POPULATION

#### 5.1 INCLUSION CRITERIA

Inclusion and exclusion criteria will be pre-screened based on information provided by the referring clinician. All inclusion and exclusion criteria will then be verified at the screening visit and official screening laboratory studies will be performed as part of that visit. There will be no birth weight or length inclusion or exclusion criteria.

In order to be eligible to participate in this study, an individual must meet all of the following criteria:

1. Parent(s) or guardian(s) are willing and able to provide written, signed informed consent after the nature of the study has been explained and prior to performance of any research-related procedure. Also, subjects under the age of 18 are willing and able to provide assent (if required) after the nature of the study has been explained and prior to performance of any research-related procedure.
2. Stated willingness to comply with all study procedures and availability for the duration of the study
3. Age  $\geq 3$  years 0 days AND  $\leq 10$  years 364 days for males,  $\leq 9$  years 364 days for females
4. Pre-pubertal defined as Tanner Stage 1 breasts in females and testicular volumes  $\leq 3$  cc in males. This must be confirmed at the Day 1 visit prior to initiation of vosoritide.
5. Patient height  $\leq -2.25$  SDS. All height SDS values are calculated using the CDC growth charts/data tables.

6. Patients with pathogenic or likely pathogenic variants in genes known to cause the specific genetic subgroups of short stature listed below are eligible for inclusion in the study. Pathogenicity of variants will be classified as per the American College of Medical Genetics criteria with the exception of *ACAN* mutations as detailed below. Documentation of the presence of the variant must be obtained using a lab results report from a CLIA certified laboratory. Classification of the variant's pathogenicity status will be performed by the Children's National study team.
- A. CNP deficiency due to mutations in *NPPC* – Subjects with heterozygous or homozygous defects in *NPPC* are eligible.
  - B. Hypochondroplasia – Subjects with heterozygous variants in *FGFR3* gene associated with hypochondroplasia are eligible. Subjects with variants in *FGFR3* known to cause achondroplasia or thanatophoric dysplasia or SADDAN syndrome will be excluded.

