### 9.2 SAMPLE SIZE DETERMINATION

This is an exploratory proof of principle Phase I/II study, and therefore, no formal sample size calculations were performed. The study size was chosen based on the feasibility of recruitment in this study time period.

Once the initial sample size of 35 subjects is achieved, we will discontinue recruitment of any genetic cohort with greater than 15 subjects. Additional recruitment efforts will then focus on achieving approximately 10 subjects in each of the cohorts.

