### 9.4 STATISTICAL ANALYSES

#### 9.4.1 GENERAL APPROACH

Analyses on all endpoints will be self-controlled, comparing measurements for each subject during follow-up to the same measurements during the baseline period. Thus, all measurements will be summarized for baseline period (control period), and during follow-up (test drug period). Descriptive statistics will be presented for all measures of change from baseline (mean, standard deviation, median, interquartile range, min and max). Comparisons between baseline period and follow-up period will use a paired t-test for continuous endpoints and a chi-square test for dichotomous endpoints. If there are departures from normality or small samples, we will use Mann-Whitney test for comparison of medians and exact Clopper-Pearson test for comparison of dichotomous endpoints.

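### The fixed paired t-test treats all children as independent, with no limit on siblings and no provision for families; if affected siblings enrol, p-values may be too small, mainly in the small genetic cohorts.

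*Protocol*

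**What the plan says.** Protocol section 9.4.1 sets the general rule: "Comparisons between baseline period and follow-up period will use a paired t-test for continuous endpoints and a chi-square test for dichotomous endpoints". For departures from normality or small samples it substitutes a Mann-Whitney test. Section 9.4.2 applies the rule to the primary endpoints: "The test of hypothesis of no change from the baseline in growth velocity and height SDS will be conducted via paired t-test". Section 9.4.3 tests the secondary endpoints in the same way, and section 9.4.7 stratifies analyses by age, sex and genetic subgroup.

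On cohort size, section 4.2 says "We propose to include up to 75 subjects in order to have at least 10 subjects in each subgroup", and section 9.2 says "Additional recruitment efforts will then focus on achieving approximately 10 subjects in each of the cohorts".

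On inheritance, section 2.2 describes short stature from NPPC variants as dominantly inherited and reports: "To date, 2 families have been identified who have heterozygous mutations in the CNP gene itself". For ACAN it states: "Individuals with heterozygous defects in Aggrecan present with dominantly inherited short stature". Section 5.1 admits NPPC subjects without a limit per family: "Subjects with heterozygous or homozygous defects in *NPPC* are eligible". For ACAN missense variants it requires either a de novo variant or segregation with short stature among available relatives. No inclusion or exclusion criterion mentions siblings, and none of the stated analyses refers to family membership.

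**The concern.** A paired t-test is a one-sample t-test on each child's change, and it is valid when those changes are independent across children. Affected siblings carry the same variant. The protocol itself lists a possible link between genetic etiology and efficacy as something to explore (section 3), so siblings may well respond alike. Pairing removes stable family differences in level. It does not remove a shared response to treatment or a shared deviation in the 6-month baseline window.

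At stake are the genotype-specific results more than the pooled one. The amendment history for version 2.8 gives evidence of efficacy within each genetic cohort as the reason for enlarging the study. In a cohort of about 10, a few families could be read as more independent evidence than they supply. The foreseeable route is ordinary: a dominantly inherited condition, no rule against relatives, and for some ACAN variants an eligibility work-up that already looks at affected relatives.

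**Working it through.** The protocol states no alpha, power, SD or intra-family correlation, so there is no figure of its own to reproduce. One arithmetic check is possible: 6 cohorts × 10 = 60, which fits within 75.

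**Inputs from the protocol:** N up to 75; six genetic cohorts; about 10 per cohort; paired t-test on the change.

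**Assumed inputs (not in the documents):** two-sided alpha 0.05; intra-family correlation of the change (ICC) 0.1, 0.3 and 0.5; 5, 10 or 20 sibling pairs among 75, and various family structures in a cohort of 10.

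**Formulas.** With family sizes m_i summing to N, the design effect is DEFF = 1 + ICC × (Σm_i²/N − 1). The true standard error divided by the naive one is about √DEFF, and the effective sample size is N/DEFF.

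**Worked example, 75 children with 10 pairs.** Σm_i² = 10×4 + 55×1 = 95, and 95/75 = 1.267. At ICC 0.5, DEFF = 1 + 0.5 × 0.267 = 1.133 and √1.133 = 1.065. The naive standard error is about 6% too small (1 − 1/1.065 = 0.061).

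**Worked example, 10 children as 5 pairs.** Σm_i² = 20, and 20/10 = 2. At ICC 0.5, DEFF = 1 + 0.5 × 1 = 1.5, √1.5 = 1.225, and the effective sample size is 10/1.5 = 6.7.

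**Simulation.** Change = family effect (variance ICC) + child effect (variance 1 − ICC), with true mean change zero. A one-sample t-test was run on the changes, with 100,000 runs per scenario. Each cell shows results at ICC 0.1 / 0.3 / 0.5.

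| Scenario | √DEFF | Type I error at nominal 0.05 |
|---|---|---|
| 75, no siblings | 1.00 / 1.00 / 1.00 | 0.050 / 0.051 / 0.052 |
| 75, 5 pairs | 1.01 / 1.02 / 1.03 | 0.051 / 0.055 / 0.058 |
| 75, 10 pairs | 1.01 / 1.04 / 1.06 | 0.054 / 0.060 / 0.066 |
| 75, 20 pairs | 1.03 / 1.08 / 1.13 | 0.056 / 0.070 / 0.082 |
| 10, no siblings | 1.00 / 1.00 / 1.00 | 0.049 / 0.049 / 0.050 |
| 10, 1 pair | 1.01 / 1.03 / 1.05 | 0.052 / 0.056 / 0.059 |
| 10, 3 pairs | 1.03 / 1.09 / 1.14 | 0.057 / 0.071 / 0.085 |
| 10, 5 pairs | 1.05 / 1.14 / 1.22 | 0.061 / 0.085 / 0.111 |
| 10, two families of 5 (extreme) | 1.18 / 1.48 / 1.73 | 0.097 / 0.196 / 0.296 |

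The rows without siblings sit at 0.05 up to simulation noise, as they should. In the pooled test the inflation is slight unless many pairs enrol. In a cohort of 10 it is slight with one pair and becomes material as the cohort comes to consist of few families.

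**The case against.** Five points can be made against this.

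- **Nothing says that siblings will enrol.** A reader might infer that the standard errors are too small as a matter of fact. The documents do not support that: with no relatives, or no correlation in the changes, the test is correct. This objection stands, and the point is therefore conditional.
- **The NPPC cohort need not be filled with siblings.** A reader might set the two known families against the target of about 10 and conclude that the cohort can hardly be filled otherwise. The protocol does not support this. It does not say that these families live in the United States, where all recruitment takes place (section 5.5), or that they have several children meeting the age and height limits. About 10 is an aim, and section 4.2 concedes: "It is difficult to predict the anticipated distribution of patients between each subgroup". The cohort may simply stay small. The row with two families of five is therefore an extreme case and should not be quoted as the expected effect.
- **An ICC of 0.5 may be generous.** Only correlation in the change matters, and annualising a six-month velocity doubles child-specific measurement error, which pulls the correlation down. This is fair, and it is why the range starts at 0.1.
- **Small cohorts may be rank-tested.** Section 9.4.1 moves small samples to Mann-Whitney, so the t-test figures for 10 children are not error rates of that procedure. That is correct. However, the rank test also assumes independent children, and the section does not say how small is small.
- **The SAP may deal with this.** The protocol defers further analysis detail to a separate SAP, so the absence of a clustered sensitivity analysis there cannot be asserted. The protocol nevertheless fixes the test itself. The topics that sections 9.4.2 and 9.4.3 name for deferral are missing data, outliers, non-adherence and loss to follow-up, not dependence between children.

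**Conclusion.** The concern holds in conditional form. The protocol fixes tests that assume independent children, does not limit enrolment to one child per family, and makes no provision for family clustering. If affected siblings enrol and their changes are positively correlated, standard errors and p-values will be too small.

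The pooled primary result is not seriously threatened under plausible sibling numbers. The genotype-specific tests are where the matter deserves attention, even though section 4.2 calls them exploratory and leaves proof of efficacy to a later randomised study. The sizes rest wholly on assumed correlations, assumed family structures and a two-sided 5% level.

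**What to change.** - Add a family identifier to the CRF.
- In sections 9.4.1 to 9.4.3, test the mean change with family-clustered, small-sample-corrected standard errors. With G families and residuals e, use the variance [G/(G − 1)] × Σ_families(Σe within family)² / N², referred to t with G − 1 degrees of freedom. When every family contributes one child, G = N and this is exactly s²/N with N − 1 degrees of freedom, which is the planned paired t-test. A random family intercept is a poorer choice for the stated method, because it cannot be separated from residual variance when no siblings enrol.
- Report the number of families beside the number of children for every genetic cohort.
- Fix in advance a minimum number of families below which a cohort is presented descriptively, without a test.
- At the least, prespecify a sensitivity analysis with one child per family.

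The cost is one CRF field, a few sentences in the protocol and SAP, and slightly wider intervals where siblings are enrolled. If no relatives enrol, the result of the planned t-test does not change.

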#### 9.4.3 ANALYSIS OF THE SECONDARY ENDPOINT(S)

Change in sitting height ratio, arm span minus standing height, and bone age/chronological age ratio from baseline to each scheduled time point will be summarized and tested similarly to the primary efficacy analyses. Additional details of the analysis including management of missing data, and approach to handling outliers, non-adherent and lost to follow up subject data will all be included in a separate statistical analysis plan.

#### 9.4.4 SAFETY ANALYSES

All subjects who receive at least one dose of study treatment in this study will be included in the end-of-study safety analysis. The end-of-study safety analysis will be descriptive.

All AEs will be categorized and classified for severity as described above based on the original terms entered on the CRF. The incidence of AEs will be summarized by system organ class, preferred term, relationship to study treatment, and severity. All AEs, including AEs that lead to dose interruption/hold, permanent discontinuation from the study and from study treatment and SAEs, will be listed.

All other safety measures including laboratory tests, vital signs, ECG, and concomitant medication data will also be summarized descriptively. Laboratory tests will also be summarized by absolute and percent change from baseline and listed by significant values.

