**Objectives:**

The primary objectives of the study are as follows:

- To evaluate the safety and tolerability of daily subcutaneous (SC) injections of vosoritide administered for 12 months in patients with selected genetic causes of short stature
- To evaluate the change from baseline in age-sex standardized annualized growth velocity after 12 months of daily SC injections of vosoritide in patients with selected genetic causes of short stature

- To evaluate the change from baseline in age-sex standardized height standard deviation score (SDS) after 12 months of daily SC injections of vosoritide in patients with selected genetic causes of short stature

The secondary objectives of the study are as follows:

- To evaluate changes in body proportions from baseline after 12 months of daily SC injections of vosoritide
- To evaluate changes from baseline in bone age/chronological age after 12 months of daily SC injections of vosoritide

The exploratory objectives of the study are as follows:

- To evaluate the pharmacokinetic (PK) profile of vosoritide in patients with selected genetic causes of short stature
- To evaluate changes from baseline in bone mineral density (BMD) after 12 months of daily SC injections of vosoritide
- To evaluate changes from baseline in vosoritide activity biomarkers and bone/collagen biomarkers after 12 months of daily SC injections of vosoritide
- To evaluate immunogenicity and assess impact on safety and efficacy measures after 12 months of daily SC injections of vosoritide
- To explore the relationship between genetic etiology and safety and efficacy
- To evaluate changes from baseline in quality of life using the QoLISSY scale after 12 months of daily SC injections of vosoritide

During the extension study, all of the primary, secondary and exploratory aims will remain the same, but the timeframe will be extended from 12 months until growth cessation or subject withdrawal from the study.

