#### **Endpoints:**

The primary study endpoints include:

- Incidence of adverse events per subject with particular attention to Grade 3 and 4 adverse events as well as to rates of hypotension
- Change from baseline in age-sex standardized annualized growth velocity after 12 months of treatment
- Change from baseline in age-sex standardized height SDS after 12 months of treatment

The secondary study endpoints include:

- Change from baseline in seated height ratio after 12 months of treatment
- Change from baseline in arm span minus standing height after 12 months of treatment
- Change from baseline in bone age/chronological age after 12 months of treatment

During the extension study, all of the endpoints will remain the same, but the timeframe will be extended from 12 months until growth cessation or subject withdrawal from the study.

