## 4 STUDY DESIGN

### 4.1 OVERALL DESIGN

We hypothesize that patients with selected genetic causes of short stature will benefit from treatment with vosoritide, a CNP analog which directly targets the growth plate. The selected genetic causes included in this study all have in vitro and in vivo evidence to suggest a prospect of benefit from vosoritide treatment.

This is a pediatric open-label, Phase I/II, single arm study of up to 75 subjects with selected genetic causes of short stature. This is a single site study being performed at Children's National Hospital. Subjects who are 3 to 10 years old inclusive for males and 9 years old inclusive for females who meet the clinical inclusion criteria defined below and meet all eligibility requirements will participate. After enrollment, subjects will be followed for a 6-month observation only period to establish a baseline height velocity, safety profile, and quality of life assessment. Vosoritide will then be administered daily via subcutaneous injection at a dose of 15 µg/kg/day for 12 months. Subjects with a positive response to therapy will be given the option to continue in the extension phase of the study during which they will continue to receive vosoritide until growth cessation.

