#### 4.4 END OF STUDY DEFINITION

A participant is considered to have completed the study if he or she has completed all phases of the study including the last visit or the last scheduled procedure shown in the Schedule of Activities (SoA), Section 1.3.

The end of the study is defined as completion of the last visit or procedure shown in the SoA in the trial globally.

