### 9.1 STATISTICAL HYPOTHESES

- Primary Safety Endpoint(s): We will rule out safety concerns. That is, we will rule out the null hypothesis that risk of adverse events post-drug administration will be more than twice the risk during the baseline period (i.e, RR or OR > 2).
- Primary Efficacy Endpoint(s): The null hypothesis is that there is no change from baseline in annualized growth velocity or height SDS over the 12 months of intervention when compared to the 6 month baseline observation period. The alternate hypothesis is that there is a change from baseline in these values.
- Secondary Efficacy Endpoint(s): The null hypothesis is that there is no change from baseline in seated height ratio, arm span minus standing height, or bone age divided by chronological age over the 12 months of intervention when compared to the 6 month baseline observation period. The alternate hypothesis is that there is a change from baseline in these values.

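### Section 9.1 sets a test for the primary safety endpoint, but 9.4.4 makes the analysis descriptive and times it at an end of study that, read directly, takes in a response-selected extension

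*Protocol*

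**What the plan says.** **Objective and endpoint (1.1 and 3).** The primary safety objective is "To evaluate the safety and tolerability of daily subcutaneous (SC) injections of vosoritide administered for 12 months". The matching endpoint is "Incidence of adverse events per subject with particular attention to Grade 3 and 4 adverse events as well as to rates of hypotension". It states no time window, whereas both primary efficacy endpoints are set at 12 months of treatment. For the extension, the same sections keep all endpoints and lengthen their time frame to growth cessation or withdrawal.

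**Hypothesis (9.1).** For primary safety, "we will rule out the null hypothesis that risk of adverse events post-drug administration" exceeds a limit. The null is that "risk of adverse events post-drug administration will be more than twice the risk during the baseline period", given as an RR or OR above 2. No window is stated for the treated period. The baseline period is 6 months (4.1: "After enrollment, subjects will be followed for a 6-month observation only period").

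**Analysis (9.4.1 and 9.4.4).** Section 9.4.1 gives a general self-controlled comparison of baseline with follow-up, using chi-square for dichotomous endpoints. Section 9.4.4 says "All subjects who receive at least one dose of study treatment in this study will be included in the end-of-study safety analysis" and "The end-of-study safety analysis will be descriptive". It summarises AE incidence and does not mention exposure time.

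**Timing (4.4, 1.3, 5.1, 9.4.6).** "The end of the study is defined as completion of the last visit or procedure shown in the SoA in the trial globally". The schedule in 1.3 includes a table for the extension. Entry to the extension requires a positive growth response in the first treatment year, with an exception for some children who had responded poorly to growth hormone. No interim analysis is planned.

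**The concern.** Two things are fixed in ways that do not fit together.

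First, 9.1 makes primary safety an inferential claim against a margin, while 9.4.4 makes the same endpoint descriptive. A descriptive summary cannot exclude a doubling of risk. An SAP that follows 9.4.4 leaves 9.1 unanswered, and an SAP that tests 9.1 departs from 9.4.4.

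Second, the only stated time for the safety analysis is the end of the study, and no 12-month cut-off is given. If that end lies in the extension, the proportion of children with an AE depends on how long each child was followed. Length of follow-up in turn depends on growth response. The resulting incidence would describe neither the 12 months in the objective nor a common period of exposure, and a comparison with the 6-month baseline would be dominated by unequal time at risk.

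**Working it through.** The protocol states no AE rate, alpha or power (9.2 reports no sample size calculation), so there is no planned figure to reproduce. The following illustrates direction and order of size only.

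**Inputs from the protocol**
- Baseline period: 0.5 year (4.1).
- Treated main phase: 1 year (1.1).
- Margin: RR or OR of 2 (9.1).
- Age at entry: from 3 years up to 10 years 364 days (boys) or 9 years 364 days (girls) (5.1).
- The extension starts 18 months after entry (1.2, 1.3).
- The extension ends at growth below 1.5 cm/year, or at bone age 13 (girls) or 15 (boys) (7.1).

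**Assumptions**
- AE rate L per child-year, constant, with no drug effect.
- A share f of children enters the extension for e years.
- Bone age tracks chronological age (used only to bound e).

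**Plausible extension length.** The youngest child starts the extension at 3 + 1.5 = 4.5 years, leaving 13 − 4.5 = 8.5 years (girl) or 15 − 4.5 = 10.5 years (boy). The oldest start at about 11.5 (girl) or 12.5 (boy), leaving about 1.5 or 2.5 years. An e of 5 years lies inside this range.

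**Formulas**
- Incidence over t years: p(t) = 1 − exp(−L·t).
- End-of-study cohort incidence: (1 − f)·p(1) + f·p(1 + e).

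**Worked case: L = 0.2, f = 0.5, e = 5**
- Baseline: p(0.5) = 1 − exp(−0.1) = 9.5%.
- 12 months: p(1) = 1 − exp(−0.2) = 18.1%.
- Child who enters the extension: p(6) = 1 − exp(−1.2) = 69.9%.
- Cohort at end of study: 0.5 × 18.1% + 0.5 × 69.9% = 44.0%.
- RR against baseline: 18.1/9.5 = 1.90 at 12 months; 44.0/9.5 = 4.62 at end of study.

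**Range.** With L from 0.05 to 1.0, f from 0.25 to 0.75 and e of 2 or 5 years, the null RR against baseline runs from 1.8 to 8.4 and the null OR from 3.0 to 15.1.

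**Does a 12-month cut alone solve it?** No. With no drug effect, 12-month against 6-month incidence gives:

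| L per year | 6 months | 12 months | RR | OR |
|---|---|---|---|---|
| 0.05 | 2.5% | 4.9% | 1.98 | 2.03 |
| 0.2 | 9.5% | 18.1% | 1.90 | 2.11 |
| 1.0 | 39.3% | 63.2% | 1.61 | 2.65 |

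Twice the time at risk nearly doubles the risk when events are uncommon. A raw comparison therefore sits close to or beyond the margin of 2 for a harmless drug. A rate ratio per person-time would be L/L = 1 under the same assumptions, as would the RR over equal 6-month windows.

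**The case against.** **A test does exist in 9.4.1, and details go to the SAP.** This stands in part. It would be wrong to say that the protocol contains no comparative test. But 9.4.1 does not test against a ratio of 2 and sets no limit on follow-up, and 9.4.4 still labels the safety analysis descriptive. The SAP can add detail, but it cannot satisfy both statements.

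**The end of study may mean the main phase.** The synopsis lists a 36-month study and, separately, an extension of up to 15 more years, so the pooling may be unintended. That is plausible. However, 4.4 defines the end through the schedule and for the trial as a whole, without separating the phases, and the schedule section includes the extension. The direct reading remains the pooled one.

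**Stronger inferences that the documents do not support:**
- A reader might infer that 9.1 itself promises a 12-month test. It does not. The 12 months come from the objective, and 9.1 names no treated window.
- A reader might infer that safety review waits for years. It does not. The DSMB receives AE reports at least every 6 months (8.3.5, 10.1.6), and the absence of an interim analysis does not by itself forbid a main-phase analysis.
- A reader might take 15 years as typical extension follow-up. The entry ages and stopping rules in 5.1 and 7.1 make such averages implausible.
- A reader might note that 4.4 counts as completers only those who finish all phases, and infer a biased analysis. No analysis uses completer status; 9.3 takes all dosed children. This is a matter of wording.

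**Conclusion.** The point holds. Sections 9.1 and 9.4.4 contradict each other on whether primary safety is tested, and the only stated analysis time, read through 4.4 and 1.3, gives a per-subject AE incidence whose follow-up is selected by growth response and not adjusted for exposure.

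The size is illustrative: from 18% to 44% incidence, and RR from 1.9 to 4.6, at 0.2 events per year with half the children entering for 5 years and no drug effect. It rests on a constant rate and on assumed entry and duration. Contact in the extension is sparser (every 3 months, against bi-weekly and then monthly calls in the treatment year), so fewer minor events may be captured and the inflation could be smaller. The direction does not depend on these values. If only the main phase was meant by end of study, the response-selected component disappears, but the conflict between 9.1 and 9.4.4 and the 12- versus 6-month imbalance remain.

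**What to change.** 1. **9.4.4 (and the AE endpoint in 1.1 and 3):** define the primary safety analysis as events from Day 1 to the Month 12 visit in all dosed children, run when the last child reaches Month 12.
2. **9.1:** choose one of two routes.
   - Make that analysis the one that answers 9.1: a within-subject ratio of AE rates per person-time, or a comparison over equal 6-month windows, with its confidence interval compared with 2. State that raw 12-month against 6-month incidence will not be used.
   - Otherwise, delete the claim to rule out a doubling and keep safety descriptive.
3. **Extension:** report AEs separately, as events per person-year.
4. **4.4:** state the end of the main phase and the end of the extension separately.

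If the comparison is kept, 8.3.1 and 8.3.4 also need to agree on pre-dose events. The first limits reporting before dosing to certain SAEs, while the second records reportable events from consent, and the baseline rate is the denominator.

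The cost is protocol and SAP wording and one additional data cut. No extra data collection is needed. With no sample size calculation in 9.2, the interval may be too wide to exclude 2, which is a reason to decide now whether 9.1 should keep its claim.
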